| Risk analysis                                                                                          | The risk-classification is assessed as low / moderate to the study population receiving study drug at the current regimen. Lanadelumab has a favorable safety profile and is approved by the Dutch medicines evaluation board for the dose administered. Therefore the risk for adverse events is low.                                                                                                                                                                                                                                                                                                                                                                                                                                                                                                                                                                                                                                                                                                          |
| Nature and extent of the burden and risks associated with participation, benefit and group relatedness | 
The study participants are COVID-19 patients that might benefit from the participation in this clinical trial.
 
Participants are on the ward of the time of study
 
Burden: short visits (15 minutes) several time per day on the ward by doctor and nurse for clinical evaluation. The duration of the entire trial (excluding screening period) is 14 days. Duration of treatment with study medication is 2 days.
 
Lanadelumab has a generally favorable safety profile. We refer to the SmPC for most common side effect.
 
For pharmacokinetic purposes 14 blood samples will be taken in total in the intervention group only. For a total of 28 mL. Additional samples will be taken for biomarker evaluation (two occasions of 40mL each).
 
Safety assessment (haematology, clinical chemistry, blood glucose tests, hCG blood and hCG urine tests, serology) will be collected as part of routine care. The total blood volume taken will be approximately 100 mL..
 |

| ANALYTICAL AND
STATISTICAL
METHODS |                                                                                                                                                                                                                         |

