### 3. Subject population

#### 3.1 Number of subjects and subject selection

Fourty patients will be randomized 1:1 for the intervention with lanadelumab iv. Twenty SARS-COV2 positive patients treated with lanadelumab 300 mg IV on day 1, followed by a second dose of lanadelumab 300 mg IV on day 4. The other 20 lanadelumab patients will receive the same treatment algorithm while NOT receiving lanadelumab. The estimated number of patients being treated for COVID disease is difficult to predict. Currently about 20% of the COVID-19 patients are hospitalized and out of these patients about 20% is admitted to the ICU.

These will be patients from the following centers:

- Amsterdam UMC, Amsterdam
- Radboud University Medical center, Nijmegen,
- University Medical Center Utrecht, Utrecht,
- Rijnstate Hospital, Arnhem
- Flevoziekenhuis, Almere

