#### 3.4 Study duration

The expected duration of the study for an individual patient will be as long as the patient is hospitalized. The estimated length of time needed to complete the entire study will be one month.

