#### 3.5 Removal of subjects from the study

The investigator may terminate participation if:

- There is violation of protocol
- It is in the best interest of the subject
- Patients that are transferred to the ICU will be followed up for safety and if possible samples will be taken, but are considered to have reached a study endpoint.

Subjects dropping out before the final dose has been given, will not be replaced. Patients are regarded evaluable after both treatment days are completed.

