### **7.3 Statistical analysis**

Statistical analysis will be performed using descriptive statistics for tabulation of population as well as results. [name] from our department of health evidence will help with the statistical analysis. Appropriate test will be deployed.

For the primary endpoint we intend to collect repeated measurements of oxygen use in L/min and therefore any significant decline in a patient's health should be reflected in these repeated measurements. We acknowledge that missing data due to death is a potential source of bias, particularly if oxygen is stopped at the point where a significant decline is observed. Therefore, a worst-case scenario sensitivity analysis, in which the highest value of oxygen recorded for any patient is imputed for patients with missing data following their death. Other valid methods to account for missing data due to death will be investigated and included in the Statistical Analysis Plan.

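### The primary oxygen endpoint (L/min) has no defined value after ICU transfer or discharge, and the protocol's missing-data text covers death only

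*Protocol*

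**What the plan says.** - **Endpoint.** Section 7.3: "For the primary endpoint we intend to collect repeated measurements of oxygen use in L/min". It adds that "any significant decline in a patient's health should be reflected in these repeated measurements".
- **Missing data.** Section 7.3: "We acknowledge that missing data due to death is a potential source of bias". The one rule given is a worst-case sensitivity analysis in which "the highest value of oxygen recorded for any patient is imputed for patients with missing data following their death". Further methods are promised for the SAP, again for death.
- **ICU transfer.** Section 3.5, under removal of subjects: transferred patients have safety follow-up, and samples where possible, "but are considered to have reached a study endpoint".
- **Discharge.** Section 3.4: "The expected duration of the study for an individual patient will be as long as the patient is hospitalized".
- **Trial length.** Synopsis, burden and risks: "The duration of the entire trial (excluding screening period) is 14 days".
- **Schedule.** Table 1 in section 6.1 lists oxygen need at inclusion, daily to day 7, on days 8-14 and after day 14, with no exception for ICU transfer or discharge. Footnote d names ICU admission as an outcome next to oxygen need. It also expresses oxygen need in litres per hour, whereas section 7.3 uses L/min.
- **ICU rate.** Section 3.1, on hospitalised patients: "out of these patients about 20% is admitted to the ICU".

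**The concern.** The usual serious decline on a COVID-19 ward is transfer to the ICU, and section 1.2 makes preventing that progression the main goal of treatment. Section 7.3 relies on the L/min series to show any decline. Section 3.5 treats the transferred patient as having reached an endpoint that section 7.3 never mentions, and oxygen is not among the things followed afterwards. At the other end, recovery leads to discharge, which ends participation under section 3.4.

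The primary series is therefore at risk of being cut by outcome on both sides. A drug that keeps patients out of the ICU leaves more sick patients in its ward average. A drug that speeds discharge takes its best values out. Both shrink the observed difference. With 20 patients per arm, a real signal could be missed for this reason alone.

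There is also a knock-on effect for deaths. If oxygen is not recorded in the ICU, the highest recorded value is limited to ward-level flow, so the imputation is not a worst case.

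**Working it through.** The protocol has no power calculation and no effect estimate to reproduce. Its sample size is called empirical.

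**1. How many patients are affected by ICU transfer**

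Inputs: 40 randomised (section 3.1); ICU rate about 20% (section 3.1); 1 of 10 transferred in the sponsor's icatibant series (section 1.2).

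- Expected transfers: 40 × 0.20 = 8 (4 per arm); 40 × 0.10 = 4 (2 per arm).
- Chance of at least one: 1 − 0.80^40 = 0.9999; 1 − 0.90^40 = 0.985.

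Discharge and death rates are not given.

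**2. How much could be lost (illustration; the model and rates are assumed)**

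Let latent oxygen need on the analysis day be normal with SD s: mean 0 in controls, mean −d on lanadelumab. Needs above u mean ICU transfer. Needs below a mean discharged. Assume the drug lowers ICU transfer from 20% to 10%.

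- u = Φ⁻¹(0.80) = 0.842.
- d = Φ⁻¹(0.90) − Φ⁻¹(0.80) = 1.282 − 0.842 = 0.440 (in units of s).
- Mean when patients outside (a, u) are deleted: μ + [φ(a−μ) − φ(u−μ)] / [Φ(u−μ) − Φ(a−μ)].
- Mean when all are kept and discharge is scored at the floor a: aΦ(a−μ) + μ[1 − Φ(a−μ)] + φ(a−μ).

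Deleting ICU patients only: control mean −0.350, lanadelumab mean −0.635, difference 0.285. That is 0.285/0.440 = 65% of the latent shift.

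Deleting both groups:

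| Controls discharged | a | Difference, both groups deleted | Difference, all kept, discharge at floor | Loss |
|---|---|---|---|---|
| 20% | −0.842 | 0.094 | 0.322 | 1 − 0.094/0.322 = 71% |
| 40% | −0.253 | 0.042 | 0.226 | 1 − 0.042/0.226 ≈ 82% |
| 50% | 0 | 0.025 | 0.182 | 1 − 0.025/0.182 = 86% |

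The floor-scored difference is the right yardstick, because oxygen flow cannot fall below zero. Measured against the unbounded 0.440, the loss would look larger (79% to 94%), but that full shift cannot be observed.

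**3. The same in L/min (all values assumed)**

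Take ICU/discharged proportions of 20%/30% in controls and 10%/50% on lanadelumab, the same ward mean in both arms, and discharge = 0.

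- Ward mean 3, ICU value 10: controls 0.2×10 + 0.5×3 = 3.5; lanadelumab 0.1×10 + 0.4×3 = 2.2; difference −1.3 L/min.
- Ward mean 4, ICU value 15: controls 0.2×15 + 0.5×4 = 5.0; lanadelumab 0.1×15 + 0.4×4 = 3.1; difference −1.9 L/min.

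The ward-only difference is 0 in both cases, which follows from assuming equal ward means. If ICU and discharge rates are equal in the arms, the difference with all kept is also 0, so nothing is hidden.

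**The case against.** The strongest reply has four parts.

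- **Recording may continue.** A reader might infer that oxygen recording stops at ICU transfer. No section says so. Section 3.5 does not forbid it, and Table 1 schedules oxygen need past day 14 without an ICU exception. This stands. What remains is that sections 3.4 and 3.5 and Table 1 do not fit together, and none of them gives the value to use. The stop at discharge is better supported.
- **No ward-only analysis is specified.** A reader might also infer that the primary analysis compares only patients still on the ward. The protocol fixes no time point, summary measure or analysis set for oxygen. Patients contribute the values recorded before they leave, and ICU admission is a listed outcome, so they do not vanish. This stands too. The deletion in the illustration is an extreme case, and a repeated-measures analysis would lose less.
- **The SAP may settle it.** Missing-data detail often belongs there, and the SAP is not shown. This stands only in part. What section 7.3 defers to the SAP is itself limited to death, and its claim that decline will show in the series conflicts with section 3.5 inside the protocol.
- **The study is small and exploratory.** It is open-label and hypothesis-generating. That lowers the stakes of any test, but proof of concept still rests on this endpoint.

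A reader might finally infer that the bias could reverse the effect. No scenario computed here does so.

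**Conclusion.** The concern holds as a protocol inconsistency with consequences for the primary endpoint. After ICU transfer or discharge a patient has no defined L/min value, the only missing-data provision is for death, and the missingness depends on outcome in both directions. About 8 of 40 patients would be affected by ICU transfer at the protocol's general rate for hospitalised patients, and about 4 at the icatibant series' rate.

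The loss of 71%, 82% or 86% is an illustration. It rests on a normal latent need, a fall in ICU transfer from 20% to 10%, assumed control discharge rates of 20%, 40% or 50%, and full deletion at one time point. It shows attenuation towards no difference when the drug works. It does not show what the trial's own analysis will lose.

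**What to change.** 1. Reconcile the synopsis (14 days), sections 3.4, 3.5 and 7.3, and Table 1 with its footnote d, including the unit (litres per hour or L/min).
2. Fix one analysis window from randomisation for all 40 patients. The 14 days already in the synopsis would serve.
3. State that oxygen need and ICU status are recorded through that window whether or not the patient goes to the ICU.
4. In the primary analysis, count ICU transfer as worse than any ward value, death as worst, and discharge off oxygen as 0 L/min. Discharge on oxygen takes the prescribed flow. A rank or ordinal comparison adjusted for baseline oxygen need is one valid way to do this, though not the only one.
5. Keep L/min summaries as descriptive results and the maximum-value imputation as a sensitivity analysis.

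The cost is mainly wording in the protocol and SAP, since oxygen need, ICU admission and clinical outcome are already scheduled. Some extra recording may be needed in the ICU, and after discharge for patients sent home on oxygen. The drawback is that a ranked result is less direct to read than a difference in L/min.

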## 8. Structured Risk Analysis

This study uses lanadelumab, which is an agent licensed for prophylaxis of hereditary angioedema. The dosages and clinical indications used in this trial are similar to the licensed dosages; therefore no potential harmful risks are expected in this cohort.

Lanadelumab will be given intravenous contrary to the licensed subcutaneous administration. This route of administration has been demonstrated safe at higher dosages than we will intend to use in primates.

The frequency of two dosages within a time frame is supported by population PK and PD modelling.

The burden of the patient is identical to studies previously performed in the same cohort (icatibant, reviewed by the ethics committee). We strongly believe the burden for the patient as well as the risk for severe adverse events is reduced to an absolute minimum.

We have chosen to perform this trial in patients that are Sars-COV2 positive as we believe they can directly benefit from this intervention. We consider the risk of this trial to be minimal. A similar approach to target the bradykinin pathway in 10 patients with COVID disease did not reveal specific serious adverse events. Furthermore, lanadelumab has been demonstrated safe in both healthy volunteers and patients with HAE at dosages that exceed the dosages proposed in this trial. The dosages used are strongly supported by modeling and simulation.

A possible risk could be introduced by administration of lanadelumab via intravenous infusion. As there are no harmful excipients used in lanadelumab formulation, and the drug is a full human monoclonal antibody, we expect the risk to be minimal as well with regards to this aspect.

The risk-classification is assessed as low to the patient population receiving study drug at the current regimens. Safety data on the use of higher dose are published and very-well defined. There is no attributable risk for the application of the study protocol to the COVID patients.

## 9. ETHICAL CONSIDERATIONS / RESPONSIBILITIES

### 9.1 Investigator Responsibilities

#### 9.1.1 *Good Clinical Practice*

The investigator will ensure that this study is conducted in full compliance with the most recent version of principles of the “Declaration of Helsinki”, ICH guidelines, or with the laws and regulations of the country in which the research is conducted, whichever affords the greater protection to the study subject.

#### 9.1.2 *Institutional Review Board (IRB)/Independent Ethics Committee (IEC) Approval*

This protocol and any accompanying material to be provided to the subject (such as advertisements, subject information sheets, or descriptions of the study used to obtain informed consent) will be submitted, by the investigator, to an IEC. Approval from the committee must be obtained before starting the study and should be documented in a letter to the investigator specifying the protocol number, protocol version, documents reviewed, and date on which the committee met and granted the approval.

Any modifications made to the protocol after receipt of IEC approval must also be submitted to the committee for approval prior to implementation.

#### 9.1.3 *Informed Consent*

It is the responsibility of the investigator to obtain written informed consent from each individual participating in this study after adequate explanation of the aims, methods, objectives, and potential hazards of the study and prior to undertaking any study-related procedures. The investigator must utilize an IEC-approved consent form for documenting written informed consent. Each informed consent will be appropriately signed and dated by the subject and the persons obtaining consent.

If, due to infection risk, obtaining written informed consent is not possible, the patient will be asked to consent verbally, with an independent witness present. This procedure and the name of the witness will be registered in the electronic patient file and identification log. At the moment it is feasible to obtain written informed consent (i.e. when the infection risk is reduced), this has to be obtained as well. A remark will be made on the written informed consent that verbal informed consent also has been given with the date of verbal informed consent.

For the historical controls asking the patient for permission in advance is not possible. This is because there is a disproportionate relationship between the time investment involved in requesting permission and the time involved in conducting the study.

#### 9.1.4 *Benefits and risks assessment, group relatedness*

For a number of reasons administration of the intravenous lanadelumab can lead to problems with administration. Pharmacokinetic properties and information about safety have only been derived from modelling and simulation.

There are currently no treatment options for patients with COVID19. As lanadelumab subcutaneous is expected to result in a substantial delay in effect due to the slow absorption, intravenous administration is important. Therefore, we want to investigate this alternative safe method to administer lanadelumab. The potential value of this research is to provide both the proof of concept as well as safety of treatment in COVID disease..

This study will be performed in patients with COVID disease as recommended by the guidelines for bioequivalence. Lanadelumab is well tolerated in other patient cohorts. There is a mild side effect profile as also

demonstrated in large phase III trials. Moreover, to limit the risk of side effects, this study is designed as two dose study.

The study participants are subjects  $\geq 18$  years. The safety and efficacy of intravenous lanadelumab in children and adolescents aged less than 18 years have not yet been established.

For pharmacokinetic purposes and safety assessment, blood samples will be collected. The total blood volume taken will be approximately 100-150 mL. During the days that blood samples will be collected for biomarker and PK-information, an intravenous cannula will be inserted to facilitate blood sampling and limit the amount of venous punctures.

#### **9.1.5 Incentives**

Subjects will receive no fee for this trial.

#### **9.1.6 Confidentiality**

The investigator must assure that subjects' anonymity will be strictly maintained and that their identities are protected from unauthorized parties. Only an identification code (i.e., not names) should be recorded on any form submitted to the sponsor and IEC. The investigator must keep a screening log showing codes, for all subjects screened and for all subjects enrolled in the study.

This information is not to be disclosed to any third party (except employees or agents directly involved in the conduct of the study or as required by law) without prior written consent from the Investigator. The investigator further agrees to take all reasonable precautions to prevent the disclosure by any employee or agent of the study site to any third party or otherwise into the public domain.

#### **9.1.7 Study Files and Retention of Records and Samples**

The investigator must maintain adequate and accurate records to enable the conduct of the study to be fully documented and the study data to be subsequently verified. These documents should be classified into 2 separate categories: (1) investigator's study file and (2) subject clinical source documents. Castor EDC will be used as datamanagement system.

The investigator's study file will contain the protocol/amendments, CRF and query forms, IEC and governmental approval with correspondence, informed consent, drug records, staff curriculum vitae and authorization forms, and other appropriate documents and correspondence.

Subject clinical source documents (usually defined by the project in advance to record key efficacy/safety parameters independent of the CRFs) would for example include subject hospital/clinic records, physician's and nurse's notes, appointment book, original laboratory reports, electrocardiogram (ECG), X-ray, pathology and special assessment reports, consultant letters, screening and enrolment log, etc.

All clinical study documents must be retained by the investigator for at least 5 years. The investigator must be notified prior to destroying any clinical study records.

After agreement of the subject, samples will be stored until 5 years after the start of this study in the laboratory of the pharmacy department of the Radboud university medical centre. The principle investigator is responsible for the storage. This material will be stored to study the pharmacokinetics or pharmacological questions of lanadelumab in the future. After this period the material will be destroyed. Whenever there is an intention to use samples during the period of 5 years for research that does not directly relate to the current research or in the case that coincidental findings can occur, the ethical commission will be consulted for permission.

### **9.1.8 Case Report Forms**

For each subject enrolled, a CRF must be completed and approved by the principal investigator or co-/sub-investigator within a reasonable time period after data collection. This also applies to records for those subjects who fail to complete the study (even during a screening period if a CRF was initiated). If a subject withdraws from the study, the reason must be noted on the CRF. If a subject is withdrawn from the study because of a treatment-limiting adverse event, thorough efforts should be made to clearly document the outcome.

### **9.1.9 Inspections**

The investigator should understand that source documents for this study should be made available to regulatory authority or health authority inspectors.

### **9.1.10 Protocol Compliance**

The investigator is responsible for ensuring the study is conducted in accordance with the procedures and evaluations described in this protocol.

### **9.1.11 Insurance Cover**

Since Radboudumc is the sponsor of this study, insurances will be arranged by the Radboudumc.

According to the Dutch law (WMO) the sponsor is obliged to have an insurance for compensation of subjects entered in clinical studies in the Netherlands who experienced study related injury or death. Therefore, Radboudumc, The Netherlands, has arranged a liability insurance, which is in accordance with article 7, subsection 6 of the WMO.

The Radboudumc also has an insurance providing cover for damage to research subjects through injury or death caused by the study (in accordance with the legal requirements in The Netherlands: Article 7 WMO and the Measure regarding Compulsory Insurance for Clinical Research in Humans).

The insurance is described in detail in the written subject information.

